### Sample Size

There is no standard procedure for determining the sample size for pilot studies as their main purpose is to obtain an estimate of the standard deviation that could be used to determine the likely effect size to inform a full trial (25). Thus, the proposed study will recruit a total of 44 participants in two groups of 18 allowing for an attrition rate of 20%. This is in line with sample size recommendations for pilot studies (26) and that used in a previous related pilot study of a workplace intervention to reduce sitting (27).

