### Randomization

To minimize contamination between groups in open plan offices, a cluster randomization approach will be used with offices being the unit of randomization i.e., randomization into either the intervention or control group will be assigned on an office basis (28). The number of clusters is projected to be approximately eight with an average cluster size of six (29). Randomization will be achieved by assigning a cluster ID to each office and clusters then being allocated to intervention or control group using an online randomization tool (https://www.randomlists.com/team-generator) by an independent researcher (30). Randomization will take place before the collection of baseline measurements and group allocation will not be disclosed to participants until the completion of baseline assessment (28).

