### Statistical Analysis

All statistical analyses will be performed using SPSS (IBM Corp, Armonk, New York, USA). Data will be assessed for normality using the Shapiro-Wilk test owing to the relatively small sample size. Linear mixed models will be used with arm and time as fixed effects, participant ID and cluster ID as random effects, and the baseline value of each variable as a covariate. An additional linear mixed model will be used to compare the effect of standing vs. sitting posture for the EMA variables at follow-up with posture and arm as fixed effects, participant ID and cluster ID as random effects, and the baseline value of each variable as a covariate. The Sidak *post-hoc* adjustment will be used to adjust for multiple comparisons in all models. Adjustments for missing data will be made using the estimated marginal means procedure of the linear mixed models. If there was a large number of non-normally distributed variables, the bias-corrected and accelerated (BCa) bootstrap method will be used to produce unbiased estimates of the confidence limits for all data (62). Data will be presented as mean and 95% confidence intervals of the bootstrapping procedure. The level of statistical significance will be *p* ≤ 0.05 for two-tailed tests. Magnitude of effects will be reported as Hedges' *g*, which is a corrected effect size based on Cohen's *d* that is suitable for use in small sample sizes of 20 or less per group to produce an unbiased estimate of the population effect size (63). The magnitude of the effect sizes will be considered to be small if they are ≥ 0.2, moderate if ≥ 0.6, and large if ≥ 1.2, using the scale proposed by Hopkins et al. (64). Adherence to the intervention will be assessed using the Wilcoxon signed rank test to compare baseline and follow-up classifications. The standardized test statistic of the Wilcoxon test will be converted to an effect statistic by dividing it by the square root of N (65), which can then be interpreted as *r* using the scales of Cohen (66) and Hopkins et al. (64).

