## Discussion

This pilot cluster-randomized controlled trial will evaluate the efficacy of a tailored workplace intervention for reducing and breaking up sitting, productivity, wellbeing and cardiometabolic risk biomarkers. The multi-component intervention protocol was designed using a participatory approach informed by the BCW and identification of intervention functions, policy categories and BCTs using the APEASE criteria to enhance the intervention's adherence and effectiveness. In addition to employing this systematic and evidence-based process for developing the intervention, further strengths of this study include the cluster-randomized design to minimize contamination between groups that are located within the same organization. The study will also be conducted within an ecologically valid office environment, thus enhancing its real-world application. Ecological momentary assessment will be used to assess temporal effects of the intervention on productivity during specific postures and work activities; this may provide important evidence to encourage changes in workplace policy and practice. Potential limitations include sample representativeness of the general office worker population as the study is being conducted only within two organizations. It will also not be possible to determine the effects of each individual strategy used as part of the intervention, which could help in determining their suitability for inclusion in occupational health promotion programmes. Furthermore, physical activity levels prior to taking blood samples will not be standardized. This may be a limitation as there is the potential for carryover effects of prior exercise on glucose and lipid levels.

In conclusion, this study will provide important evidence regarding the efficacy of a systematically developed tailored workplace intervention. This will include evaluating the effects of the intervention on a range of health and work-related outcomes, including an ecological momentary assessment of productivity that has been seldom employed in office workplace studies; this may be key in promoting the adoption and implementation of such interventions in workplace practice and policies. The findings of this study can be used to inform a future fully powered RCT to determine the effectiveness of this multi-component intervention for reducing sitting and improving health in office workers.

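### The pilot's size rests on estimating an SD and on precedent, yet the plan tests at p ≤ 0.05 and promises important evidence of efficacy

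*Protocol article*

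**What the plan says.** Sample Size (protocol article) says of pilot studies that "their main purpose is to obtain an estimate of the standard deviation that could be used to determine the likely effect size" for a full trial. From this it concludes that "the proposed study will recruit a total of 44 participants in two groups of 18 allowing for an attrition rate of 20" per cent, and adds: "This is in line with sample size recommendations for pilot studies". It also cites an earlier related pilot. It gives no target difference, power or intracluster correlation. Randomization adds: "The number of clusters is projected to be approximately eight with an average cluster size of six".

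The other sections point towards efficacy. The Abstract and the end of the Introduction list efficacy among the aims, next to feasibility. Workplace sitting time is the primary outcome, and feasibility and acceptability come under the secondary measures. Statistical Analysis states: "The level of statistical significance will be *p* ≤ 0.05 for two-tailed tests". It also grades Hedges' g as small from 0.2, moderate from 0.6 and large from 1.2. The Discussion concludes that "this study will provide important evidence regarding the efficacy of a systematically developed tailored workplace intervention" and links the results to adoption in workplace practice and policy. The limitations listed there do not include imprecision or the small number of offices.

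**The concern.** The reason given for the sample size and the conclusion promised from it do not match. A study sized to estimate an SD has no designed ability to separate a useful effect from none. Under a significance rule, a result above 0.05 is easily taken as absence of effect. A result below 0.05 comes from the upper part of a wide sampling distribution, so the estimate tends to be too large when the true effect is small or moderate. Employers and policy makers are the stated audience for these findings.

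The Sample Size wording is also loose. An SD scales a difference into a standardised effect but does not supply the difference.

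**Working it through.** **The plan's own figure.** 18 × 1.2 = 21.6, rounded up to 22 per arm, gives 44. Dividing by the retained fraction gives 36 / 0.8 = 45. The gap is trivial and is not the point here. With 44 enrolled and 20% lost, 44 × 0.8 = 35.2 complete, or 17.6 per arm. The 18 per group cannot be reproduced, because no power inputs are given.

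**Inputs.** From the article: 17.6 completers per arm, about 8 offices, two-sided 0.05, and thresholds for g of 0.2, 0.6 and 1.2. Completers per office are 36 / 8 = 4.5. Assumed, because the article gives neither: ICC 0 to 0.10 and baseline-to-follow-up correlation r 0 to 0.7.

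**Precision.** In SD units, SE = √[(2/17.6) × (1 + 3.5 × ICC) × (1 − r²)].
- Favourable (ICC 0, r 0.7): √(0.1136 × 1 × 0.51) = 0.241.
- Unfavourable (ICC 0.10, r 0): √(0.1136 × 1.35 × 1) = 0.392.

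The t multiplier is 2.036 on 2 × 17.6 − 3 = 32.2 df, or 2.447 on 8 − 2 = 6 df if offices set the degrees of freedom. The detectable effect is (t for 97.5% + t for 80%) × SE, where the second term is 0.853 or 0.906.

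| | Favourable | Unfavourable |
|---|---|---|
| 95% CI half-width, 32 df | 0.49 | 0.80 |
| 95% CI half-width, 6 df | 0.59 | 0.96 |
| Detectable with 80% power, 32 df | 0.70 | 1.13 |
| Detectable with 80% power, 6 df | 0.81 | 1.31 |
| Power at 0.6, 32 df / 6 df | 68% / 55% | 32% / 25% |
| Power at 0.2, 32 df / 6 df | 12% / 10% | 7% / 6% |

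Power comes from the noncentral t distribution. Even the most favourable detectable effect, 0.70, exceeds the plan's moderate threshold.

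**On the plan's own scale.** Take an observed g of 0.6 with 18 per arm, no clustering and no baseline adjustment. SE = √(2/18 + 0.36/72) = 0.341, so the interval is −0.07 to 1.27, from trivial to large. At the most favourable half-width, 0.6 ± 0.49 is 0.11 to 1.09, from trivial to moderate.

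**Size of significant estimates.** In 100,000 simulated trials with 18 per arm, a true effect of 0.5, no clustering and no adjustment, 31% were significant and their mean g was 0.89. With r = 0.7 and no clustering (17.6 per arm, normal estimates), 52% were significant with mean 0.68. The tendency persists but weakens as precision improves.

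**What the pilot estimates better.** For a pooled SD on 34 df, ignoring clustering, the 95% limits are √(34/51.97) = 0.81 and √(34/19.81) = 1.31 times the estimate. Squared, these are 0.65 and 1.72 in a planned sample size. An ICC is much less certain. With 8 offices of 4.5 and a true ICC of 0.05, its approximate SE is 0.95 × 1.175 × √[2/(4.5 × 3.5 × 7)] = 0.15, three times the ICC itself.

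**The case against.** The study calls itself a pilot, and pilots may be small. The size does not rest on the SD alone, since pilot recommendations and an earlier pilot are cited too. Statistical Analysis already plans 95% confidence intervals and effect sizes, and the Discussion leaves effectiveness to a later, fully powered trial. Large effects are within reach: at 18 per arm, without clustering or baseline adjustment, power is 94% at 1.2 SD. The Introduction cites earlier reductions of 45 to 83 minutes per shift. If the SD is 60 to 100 minutes (an assumption), power for 83 minutes is 68 to 98% without clustering, or 44 to 84% at ICC 0.10 with 6 df.

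All of this stands and narrows the point. It does not remove it. The precedents are not offered as a basis for power. The planned intervals sit beside a significance rule with nothing to say that results are preliminary. The Discussion promises efficacy evidence in the same paragraph that defers effectiveness. For 45 minutes, under the same assumptions, power is only 26 to 59%, or 16 to 37% with clustering.

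Four stronger readings are tempting but unsupported:
- **That the full trial will be powered on the pilot's g.** Sample Size makes a general remark about pilots, which can mean scaling a chosen difference by the SD. The Discussion says only that findings can inform a later trial.
- **That non-significance will be reported as no effect.** No such rule is stated.
- **That every significant result will be an overestimate.** It is a tendency at low power and matters little for a large true effect.
- **That more participants should be enrolled.** The mismatch lies in the conclusion claimed, not in the number.

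**Conclusion.** The point holds as a mismatch between the basis for the sample size and the efficacy conclusion the article promises. Under the assumed ICC and baseline correlation, half-widths are about 0.5 to 0.8 SD (0.6 to 1.0 with 6 df) and detectable effects about 0.7 to 1.1 SD (0.8 to 1.3 with 6 df).

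A true effect of 0.2 would be missed roughly nine times in ten. One of 0.6 would be missed more often than not over most of the range. The exception is a strong baseline correlation, near 0.7, where the chance of detection is about even and at best about two in three. Testing is therefore unreliable for small and moderate effects, and not futile for large ones.

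No data collection or model is invalidated. The wording should be changed because it governs what may be concluded.

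**What to change.** - **Statistical Analysis and Discussion:** state that between-arm results are preliminary estimates with 95% confidence intervals, and that neither p ≤ 0.05 nor p > 0.05 supports a conclusion on efficacy. Add imprecision and the small number of offices to the limitations.
- **Abstract and Introduction:** reword the efficacy aim to match, for example as obtaining preliminary estimates of effect. Sitting time can stay as the main effect measure.
- **Sample Size:** say that the pilot supplies the SD with its confidence limits. Any office ICC is reported with its confidence interval and not used alone for planning. The full trial's target difference will be a worthwhile reduction in sitting, not the pilot's g.

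Nothing changes in recruitment, measurement or modelling. The cost is that the article's claims become less favourable.

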## Ethics Statement

The studies involving human participants were reviewed and approved by the University of Bedfordshire Institute for Health Research Ethics Committee. The patients/participants provided their written informed consent to participate in this study.
